### The Insight Platform

#### Overview

The Insight mHealth platform was developed by the mHealth Shared Resource at the University of Oklahoma Health Sciences Center and the Stephenson Cancer Center. This platform offers resources to help researchers build, test, and launch technology-based assessment and intervention tools [66]. The mHealth resource uses a sizeable team that includes 1 program manager, 4 project coordinators, and 4.5 computer scientists or engineers. Together, they develop and maintain web and mobile apps and relational databases. These apps are developed using cutting-edge, cross-platform design tools.

#### Smartphone Training

Our team has developed and implemented a brief user-friendly training protocol to aid those with limited smartphone experience. During the randomization call, all participants, depending on condition assignment, receive training on how to use either the MASP+ app or the EMA-only Insight app and the QuitGuide app. Both versions of the Insight app (MASP+ and EMA only) contain an “App Instructions” button to remind participants of how each app feature functions (Figure 2). In previous studies, similar protocols have resulted in high EMA compliance rates (eg, 82%-87% of all EMAs completed) in samples of socioeconomically disadvantaged and nondisadvantaged adults [55,65,95,96]. All smartphones used in this study automatically collect data on intervention delivery (eg, number of times features are used and number of minutes treatment videos are watched).

### Data Analyses

#### Overview

To test the hypothesis that MASP+ produces higher rates of smoking abstinence compared to the NCI QuitGuide app, a biochemically verified measure of 7-day PPA that is collected during weekly assessments via Bedfont iCO will be used. PPA is defined as no smoking, not even a puff, in the 7 days before follow-up assessments and biochemical verification of smoking abstinence (ie, CO levels <7 ppm according to an iCO test). We will calculate odds ratio effect sizes (with 95% CI) to estimate between-group differences for PPA at each follow-up assessment. The effect size for the comparison between conditions at the 26-week postquitting date assessment will serve as the primary analysis of the impact of treatment condition on smoking cessation.

We will then conduct a series of conditional latent growth curve models (LGM) to examine the impact of treatment condition on abstinence trajectories. First, an LGM will be specified using CO breath tests at 2 (quit date), 3, 4, 5, 6, and 28 weeks. The intercept of these models will be centered on the baseline assessment and will be specified to model linear change across the major assessments. A dummy code representing the treatment condition will be specified as a predictor of the intercept and slope factors to quantify the effect of MASP+ on the longitudinal course of abstinence.

The impact of treatment conditions on HIV quality of life, ART adherence, and HIV treatment engagement (hypothesis 2) will be examined using the same sequence of analyses: between-condition effect sizes followed by conditional LGM. We will then conduct univariate LGM to explore changes in AS a function of treatment (hypothesis 3), followed by a series of parallel process LGM to examine how changes in AS relate to changes in smoking and HIV outcomes. The indirect effects of treatment via AS will be evaluated by calculating bootstrapped CIs of the indirect effect using the MODEL INDIRECT command in MPlus.

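### The growth model said to measure the course of abstinence is specified on CO breath tests, not on the protocol's two-part abstinence outcome, so as written it estimates smoke exposure

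*Protocol article*

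**What the plan says.** All of this stands in the protocol article, Data Analyses, Overview.

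- The outcome has two parts: "PPA is defined as no smoking, not even a puff, in the 7 days before follow-up assessments and biochemical verification of smoking abstinence", the verification being "CO levels <7 ppm according to an iCO test".
- Odds ratios with 95% CIs are planned for this outcome at every follow-up, and "The effect size for the comparison between conditions at the 26-week postquitting date assessment will serve as the primary analysis" of treatment on cessation.
- A second step adds "conditional latent growth curve models (LGM) to examine the impact of treatment condition on abstinence trajectories".
- The variable and occasions of the first such model are named: "First, an LGM will be specified using CO breath tests at 2 (quit date), 3, 4, 5, 6, and 28 weeks". No cut-off and no self-report component is attached to it.
- On its form: "The intercept of these models will be centered on the baseline assessment and will be specified to model linear change across the major assessments".
- Treatment condition enters as a "predictor of the intercept and slope factors to quantify the effect of MASP+ on the longitudinal course of abstinence".

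Elsewhere, Recruitment and Procedures gives the CO device the role of verifying self-reported abstinence at follow-up. Smoking Outcomes describes CO as a validated indicator of smoking status.

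**The concern.** The question, the variable and the interpretation do not match. The question and the interpretation concern abstinence, which the protocol makes a binary, two-part outcome. The variable is one of those parts. CO falls when people who still smoke cut down, and someone who reports smoking can read below 7 ppm. Among continuing smokers CO varies widely, and that spread says nothing about who has quit.

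Followed literally, the model could report a benefit on abstinence with no extra quitters, or miss one that exists. Sample Size Determination says conclusions will rest mainly on effect sizes and CIs, which will guide larger trials. The practical harm is therefore a mislabelled and diluted effect size more than a formal wrong rejection. Objectives also hypothesises that change in anxiety sensitivity mediates smoking abstinence. If the parallel process models reuse the CO series, they would answer that question for smoke exposure.

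**Working it through.** The protocol gives no CO distribution, abstinence rate or power figure for this model, so there is no plan figure to reproduce. Everything below except the design is an assumption.

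**Inputs.** From the document: N = 72, weeks 2, 3, 4, 5, 6 and 28, cut-off 7 ppm, linear growth with treatment predicting intercept and slope. Assumed: 36 per arm (the ratio is not stated), complete data, smokers' mean CO 18 ppm (log-SD 0.45 between and 0.35 within person), 20% lower after the quit date in both arms, abstainers' CO about 2.5 ppm, nobody abstinent at week 2, truthful self-report.

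**Step 1: what mean CO measures.** With p the abstinent share, mean CO = p × (abstainers' CO) + (1 − p) × (smokers' CO). Smokers' post-quit CO is 18 × 0.80 = 14.4 ppm.

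- *Equal quitting (15% each), MASP+ smokers 30% lower:* control 0.15 × 2.5 + 0.85 × 14.4 = 12.6; MASP+ 0.15 × 2.5 + 0.85 × 10.08 = 8.9. Difference 3.7 ppm, none of it abstinence.
- *True quitting, 10% v 30%, equal cutting down:* control 0.10 × 2.5 + 0.90 × 14.4 = 13.2; MASP+ 0.30 × 2.5 + 0.70 × 14.4 = 10.8. Difference 2.4 ppm.
- *Masking:* the second difference vanishes if control smokers' CO is (10.83 − 0.25)/0.90 = 11.8 ppm, about 18% below 14.4.

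A 20-point gain in abstinence thus moves mean CO less than a 30% cut among people who did not quit.

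**Step 2: simulation.** There were 4,000 trials per scenario. Each person's least-squares intercept and slope were compared between arms with Hotelling's T² (2 df, two-sided 5%), an approximation to the linear growth model with balanced data. With equal quitting and equal cutting down, rejection is 4-5% for every variable.

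| Scenario, joint test | CO in ppm | log CO | CO <7 only | Verified PPA |
|---|---|---|---|---|
| 15% abstinent in both arms, MASP+ smokers' CO 30% lower | 49% | 43% | 40% | 5% |
| 10% v 30% abstinent | 18% | 39% | 40% | 73% |

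With MASP+ smokers' CO 15% lower and equal quitting, rejection is about 10-13%. Dichotomising CO at 7 ppm does not cure the problem, because the self-report part is still missing.

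**Step 3: slope alone.** The protocol names no joint test. The slope test by itself gives about 8-10% against 6% with PPA in the first scenario, and 6-10% against 13% in the second. Most of the joint signal therefore sits on the baseline-centred intercept.

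**Step 4: a second set-up.** Here smokers' mean CO is 18 ppm with between-person CV 0.5, and control abstinence falls from 25% to 15%. In the first two rows abstinence is equal in both arms.

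| Scenario, joint test | CO in ppm | Verified PPA |
|---|---|---|
| MASP+ smokers cut CO by 15% | 13% | 5% |
| MASP+ smokers cut CO by 30% | 46% (slope alone 17%) | 5% |
| 35% v 15% abstinent at week 28 | 18% | 42% |
| Same quitting, QuitGuide smokers cut CO by 15-30% | 6-7% | 43% |

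A maximum-likelihood growth model on CO with free residual variances gave 50% at the 30% cut and 21% for true quitting. A logistic GEE on PPA gave 3% and 37%.

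**The case against.** **Shorthand.** The Overview opens by describing PPA itself as collected through the CO device, so the phrase about breath tests could stand for CO-verified abstinence at those weeks. It also announces a series of models, of which this is the first. That reading is possible but nowhere stated. It is too strong to infer that the authors have certainly replaced PPA with ppm; what can be said is that the text names one variable and interprets another.

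**Safeguards.** The odds ratios at each follow-up show verified abstinence wave by wave, so a conflict with the CO model would be visible. This stands. A reader might infer that the trial's abstinence conclusion is compromised; the documents do not support that, because the primary analysis uses PPA.

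**Size.** Rejection rates suit a pilot poorly, the joint test is not in the protocol, and all inputs are assumed. False signals need cutting down to differ by arm, and NRT goes to both. The first three points stand. On the last, Study Conditions gives the arms different NRT ordering routes, and NRT advice to MASP+ only, so a difference is plausible in either direction but not shown. PPA is not immune either: if 30% or 50% of smokers reading below 7 ppm report no puff, its joint rejection rises to 10.5% or 18%.

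**Remedy.** A logit or probit growth model was not itself simulated; the GEE supports only the direction. At 15% abstinent there are about 5 quitters per arm (0.15 × 36 = 5.4), and dropping the random slope would hamper models that relate change to change. This is a real trade-off, so binary PPA should not be required in the parallel process models.

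**Conclusion.** The mismatch holds on the text. The protocol says the model serves "to quantify the effect of MASP+ on the longitudinal course of abstinence", but the variable named is CO. As written, this secondary analysis estimates smoke exposure and cannot by the protocol's own definition be read as an abstinence result.

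The direction is robust across both set-ups; the size is not. It depends on assumed CO spread, on how far cutting down differs between arms, and on a joint test that the protocol does not specify. On the slope alone the distortion is small under the main assumptions.

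A reader might also infer that the mediation analysis is wrong. The document says only that changes in smoking will be modelled there and does not name the variable, so that consequence is conditional.

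**What to change.** In Data Analyses, Overview, second paragraph:

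1. Fit the abstinence trajectory model to the binary CO-verified 7-day PPA already computed at each follow-up, with a logit or probit link, on the post-quit waves. State that a random intercept only will be used if data are sparse.
2. Report any CO growth model separately, preferably on log CO, as smoke exposure and not as evidence on abstinence.
3. Name the smoking variable in the parallel process models. If CO is kept because a binary growth process is too sparse with 72 participants, label the result as mediation of smoke exposure, not of abstinence.

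If the phrase was shorthand for verified abstinence, saying so and stating the link function settles the point. At minimum, relabel the CO model.

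The cost is a rewritten paragraph and a categorical-outcome growth model. No new data are needed, since the wave-by-wave odds ratios already require the indicator. The downside is that few quitters may force a simpler random-effects structure.

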Upon completion of the baseline survey and receipt of the baseline package, the participants complete a randomization call with the study staff. During the randomization call, the participants are randomized to receive the MASP+ or QuitGuide interventions based on the randomization chart developed by the study statistician ([name]). Block randomization was used and stratified according to binary sex (assigned at birth). Variable-sized permuted block randomization (block sizes vary from 4 to 12) is used. Before data analyses, the balance of randomization will be checked and controlled for imbalanced factors by including any factors that differ between groups as covariates. The participants are provided with a unique code to access the app to which they are randomized. MASP+ participants have access to all MASP+ features (ie, Treatment Videos, Coping Toolkit, Quit Tips, and Stress Management Trainings) through the Insight platform. Participants randomized to the control intervention (ie, QuitGuide) have access to limited features (ie, App Instructions, Payment Tracking, Call Staff, and Record Stress) through the Insight platform and receive intervention content (ie, Track My Craving, Manage My Mood, and Learn To Quit) through the QuitGuide app. Participants assigned to the control intervention receive assistance with downloading the QuitGuide app through the Google Play Store. Both intervention groups use the Insight app to complete the study assessments, which include the baseline survey, weekly follow-ups, the 28-week follow-up, and EMAs. Once the code is entered, the research staff orients the participant to the app features and the iCO carbon monoxide (CO) breath testing device. Participants have access to MASP+ or QuitGuide content through the final follow-up (ie, the 28-week follow-up). At the end of the randomization call, participants are directed to take a brief postrandomization survey, which must be completed within 6 days after the randomization call. Failure to complete the postrandomization survey within 6 days does not affect participants’ status in the study.

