### Sample Size Determination

As this is the first empirical evaluation of the MASP+ intervention in this population, our focus is on determining the feasibility of the new intervention and obtaining preliminary estimates of effect sizes on smoking and HIV outcomes and the hypothesized mechanism of change, rather than conducting a full-scale and statistically powered examination of comparative efficacy. We expect that MASP+ will be superior to the NCI QuitGuide on all outcomes examined, but that the effects of MASP+ may vary and be larger for smoking outcomes than for HIV outcomes. On the basis of power calculations conducted using Repeated Measures and Sample Size and simulation studies identifying the sample sizes necessary to detect indirect effects [105,106], a target sample size of 72 would provide sufficient statistical power to detect a medium to large effect (Cohen *d*≥0.6) and an indirect effect for H3 if the treatment effect on AS is large (Cohen *d*=0.8) and the effect of AS on outcomes is medium to large (Cohen *d*=0.5). Our conclusions will primarily be based on effect sizes and associated CIs, and the effect size estimates (and associated CIs) from this trial will be used to guide future larger trials of comparative efficacy.

Qualitative interviews are conducted with all MASP+ and QuitGuide participants. The recommended minimum size for any subgroup is 20 interviews [107]. However, based on our prior work [48], interviews vary substantially in the content provided, so interviews will be conducted with all enrolled study participants in MASP+ and QuitGuide to meet the saturation of key study questions. Interviewing all MASP+ participants should be sufficient for the saturation of key study questions. The QuitGuide interviews will be used as a comparative group following the analysis of the MASP+ content, based on our prior work.

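### HIV-outcome growth models: treatment predicts an intercept measured before randomisation, which costs precision on the slope contrast but not validity

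*Protocol article*

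**What the plan says.** Under Data Analyses, Overview, the protocol article describes conditional latent growth models. On the time origin and shape it says: "The intercept of these models will be centered on the baseline assessment and will be specified to model linear change across the major assessments". On treatment it says: "A dummy code representing the treatment condition will be specified as a predictor of the intercept and slope factors". Those sentences are written for the abstinence model. For HIV quality of life, ART adherence and treatment engagement the same section says the effect of treatment "will be examined using the same sequence of analyses: between-condition effect sizes followed by conditional LGM".

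Recruitment and Procedures fixes the order of events: "Upon completion of the baseline survey and receipt of the baseline package, the participants complete a randomization call". Table 2 lists the HIV scales at baseline, week 6 and week 28. Recruitment and Procedures also provides for a balance check before analysis, with factors found to differ between the arms entered as covariates.

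**The concern.** The HIV scales have a wave collected before anyone is assigned. At that wave the arms can differ only by chance, so the treatment effect on a baseline-centred intercept is known to be zero. As carried over, the specification estimates it.

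This has two consequences. First, the slope contrast no longer borrows the information that both arms start from the same expected level, so its variance is larger than it need be. Second, it subtracts the observed baseline gap in the manner of a change score. A chance gap in favour of one arm then pulls the estimated slope effect against that arm through regression to the mean. The growth model is a planned analysis for hypothesis 2, and the target is 72 participants in a population the article itself expects to be hard to recruit. Precision obtainable from data already collected is therefore worth having.

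**Working it through.** **Inputs**
- From Sample Size Determination: 72 participants (equal arms assumed, n=36 each) and d=0.6, placed at week 28.
- From Table 2: HIV waves at 0, 6 and 28 weeks. Scaled by 28, t = 0, 0.2143, 1. So Σt = 1.2143, (Σt)² = 1.4745, Σt² = 1.0459, mean t = 0.4048.
- Not given in the article, so assumed: two-sided 5%, total variance 1, compound symmetry with correlation ρ from 0.3 to 0.8, linear truth, no dropout.

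**1. The plan's own figure.** The article calls 72 sufficient for d≥0.6 but states neither power nor alpha. At one time point, power is Φ(0.6×√18 − 1.96) = Φ(0.586) = 72.1% two-sided, or 81.6% one-sided. Averaging two follow-ups at ρ=0.5 gives 83.6%. The claim is plausible under a repeated-measures calculation and can be neither confirmed nor refuted.

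**2. Variance of the treatment-on-slope effect (per 28 weeks)**
- Intercept path free: 2(1−ρ)/(n·S), with S = Σt² − (Σt)²/3 = 1.0459 − 0.4915 = 0.5544.
- Intercept path fixed at zero: 2(1−ρ)/(n·B), with B = Σt² − ρ(Σt)²/(1+2ρ).

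As ρ approaches 1, ρ/(1+2ρ) approaches 1/3 and the two agree, which is why the gain disappears at high correlation.

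Worked at ρ=0.5:
- Free: 1/(36×0.5544) = 0.0501.
- Fixed: B = 1.0459 − 0.25×1.4745 = 0.6773, giving 1/(36×0.6773) = 0.0410.
- Power is Φ(0.6/SE − 1.96): 76.4% free and 84.2% fixed.

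| ρ | Variance, free | Variance, fixed | Cut | Power, free | Power, fixed |
|---|---|---|---|---|---|
| 0.3 | 0.0701 | 0.0505 | 28% | 62.0% | 76.1% |
| 0.5 | 0.0501 | 0.0410 | 18% | 76.4% | 84.2% |
| 0.7 | 0.0301 | 0.0271 | 10% | 93.3% | 95.4% |
| 0.8 | 0.0200 | 0.0188 | 6% | 98.9% | 99.2% |

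**3. Other covariance structures.** Under the random intercept-and-slope structures tried, the free-to-fixed variance ratio ran from 1.03 to 1.31, with power gains of about 1 to 11 points.

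**4. Effect of a chance baseline gap.** The SE of the baseline difference is √(2/36) = 0.236 SD. In the free model the estimate moves by −(1−ρ)×0.4048/0.5544 per SD of gap.
- At ρ=0.5 this is −0.365, so a one-SE gap in favour of MASP+ shifts 0.60 by −0.086, to about 0.51.
- At ρ=0.7 it is −0.219, a shift of −0.052, to about 0.55.
- In the fixed model the shift is zero, because t=0 at baseline.

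A 20,000-run simulation, looking at gaps of 0.20 to 0.27 SD, gave 0.52 and 0.55 for the free model and about 0.60 for the fixed one. Averaged over all runs, both models returned about 0.60.

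**5. Anxiety sensitivity.** With waves 0 to 6 and 28 and compound symmetry at ρ=0.5, power moves only from 86.9% to 88.7%.

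**The case against.** Letting treatment predict both intercept and slope is the ordinary conditional growth model. It is unbiased on average, its type I error is unaffected, and path-level constraints may be left to a full analysis plan. That stands against calling this an error. It does not remove the point, because the article itself states the path and the centring, and the criticism is of that choice.

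Four stronger readings are tempting, and the document does not support them.

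- **That baseline differences go unadjusted.** The free intercept absorbs the baseline gap and the slope compares change. What is missing is ANCOVA-type adjustment. The imbalance rule in Recruitment and Procedures helps somewhat, but it depends on an observed difference and does not name baseline outcomes. Where no imbalance is noted, the loss of precision remains.
- **That the affected interval is the one used to plan the next trial.** Sample Size Determination refers to effect sizes and their CIs. Data Analyses lists between-condition effect sizes as a step before the growth models and does not say the slope interval fills that role. The article also disclaims a fully powered comparison.
- **That the anxiety-sensitivity model has the same stated path.** The article announces only a univariate growth model there. The path is inferred and the gain is small.
- **That the abstinence model is affected in the same way.** Its listed waves start at week 2, so it has no baseline observation to use.

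Even for the HIV outcomes, the carry-over is a reading of a phrase that repeats the sequence and type of analysis without restating paths. It is the natural reading, but still a reading.

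**Conclusion.** The point holds for the HIV-outcome growth models as a matter of efficiency. The plan spends a parameter on a quantity that randomisation makes zero. The cost depends on a correlation the article does not give: material at low to moderate values (about 14 power points at 0.3, 8 at 0.5) and minor at high ones (2 at 0.7, 0.3 at 0.8). The tilt from a one-SE baseline gap is under 0.1 SD, against a slope SE of about 0.22 at ρ=0.5. All figures assume 36 per arm, complete data, linear change, two-sided 5% and, for the table, compound symmetry. For quality of life they also presuppose a score that is comparable over time, since Table 2 shows 36 items at baseline and 8 at later waves. Nothing here makes the planned estimate invalid.

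**What to change.** In Data Analyses, for the models of HIV quality of life, ART adherence and treatment engagement:

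- Fix the treatment-to-intercept path at zero at the pre-randomisation baseline.
- Keep the intercept-slope covariance free.
- Take the treatment effect from the slope (or post-baseline) terms.

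An alternative is to adjust for each outcome's baseline value regardless of observed imbalance, with baseline then serving as covariate rather than outcome. For quality of life, use only the items given at both baseline and follow-up. The same constraint may be applied to the anxiety-sensitivity model for consistency, with little gain expected.

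The cost is one constraint in the model code and one sentence in the plan, with no new data. The downside is that the model no longer estimates a baseline difference between arms, which is reported descriptively instead.
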